## Abstract

**Background:**

Nowadays, evaluation of the efficacy and the duration of treatment, in context of monitoring patients with solid tumors, is based on the RECIST methodology. With these criteria, resistance and/or insensitivity are defined as tumor non-response which does not allow a good understanding of the diversity of the underlying mechanisms. The main objective of the OncoSNIPE® collaborative clinical research program is to identify early and late markers of resistance to treatment.

**Methods:**

Multicentric, interventional study with the primary objective to identify early and / or late markers of resistance to treatment, in 600 adult patients with locally advanced or metastatic triple negative or Luminal B breast cancer, non-small-cell lung cancer or pancreatic ductal adenocarcinoma. Patients targeted in this study have all rapid progression of their pathology, making it possible to obtain models for evaluating markers of early and / or late responses over the 2-year period of follow-up, and thus provide the information necessary to understand resistance mechanisms. To explore the phenomena of resistance, during therapeutic response and / or progression of the pathology, we will use a multidisciplinary approach including high-throughput sequencing (Exome-seq and RNAseq), clinical data, medical images and immunological profile by ELISA. Patients will have long-term follow-up with different biological samples, at baseline (blood and biopsy) and at each tumoral evaluation or tumoral progression evaluated by medical imaging. Clinical data will be collected through a dedicated Case Report Form (CRF) and enriched by semantic extraction based on the French ConSoRe (Continuum Soins Recherche) initiative, a dedicated Semantic Clinical Data Warehouse (SCDW) to cancer.

The study is sponsored by Oncodesign (Dijon, France) and is currently ongoing.

**Discussion:**

The great diversity of intrinsic or acquired molecular mechanisms involved in resistance to treatment constitutes a real therapeutic issue. Improving understanding of mechanisms of resistance of cancer cells to anti-tumor treatments is therefore a major challenge. The OncoSNIPE cohort will lead to a better understanding of the mechanisms of resistance and will allow to explore new mechanisms of actions and to discover new therapeutic targets or strategies making it possible to circumvent the escape in different types of cancer.

**Trial registration:**

Clinicaltrial.gov. Registered 16 September 2020, https://clinicaltrials.gov/ct2/show/NCT04548960?term=oncosnipe&draw=2&rank=1 and ANSM ID RCB 2017-A02018-45.

## Background

Precision medicine is considered to be one of the major issues in patient care. A lot of researches have already proven successful implementation of targeted therapies including immunotherapies that offers to patient’s improved response and survival rates. But despite these major therapeutic advances, resistance to anti-cancer treatment is a major obstacle in the care of patients (1,2). Indeed, to date, many patients still die of cancer with 9.6 million deaths worldwide in 2018. Nowadays, improving understanding of mechanisms of resistance of cancer cells to anti-tumor treatments is therefore a major issue. The great diversity of molecular mechanisms involved in the phenomena of resistance to treatment, whether intrinsic (de novo, or primary) or acquired (secondary), constitutes a real therapeutic challenge (3, 4, 5). Indeed, a better understanding of the mechanisms of resistance would make it possible to explore new therapeutic strategies making it possible to circumvent these phenomena of escape in different types of cancer. The OncoSNIPE project was developed in this context. The objective of this project is to identify early and / or late markers of resistance to treatment in 3 different pathologies affected with resistance issues: triple negative breast cancer or Luminal B, locally advanced or metastatic non-small-cell lung cancer and pancreatic ductal adenocarcinoma (PDAC). In this project, in order to best cover the diversity of mechanisms involved in these resistances, we propose a multidisciplinary approach with clinical, genomic, transcriptomic and immunological dimensions.

## Methods/ Design

### Study population

Adult patients with a diagnosed triple negative or Luminal B breast cancer, locally advanced or metastatic non-small-cell lung cancer or PDAC and managed at Georges-François Leclerc Cancer Center (Dijon), Curie Institute (Paris), Paoli Calmettes Institute (Marseille), Haute-Pierre Hospital (Strasbourg), Godinot Institute (Reims), Léon Bérard Center (Lyon), Lorraine Cancer Institute (Nancy), APHP-Beaujon Hospital (Clichy), F-Mitterand Dijon-Bourgogne University Hospital Center (Dijon), La Miletrie University Hospital Center (Poitiers) and Besancon University Hospital Center (Besançon).All inclusion and exclusion criteria are described in Table 1.

**Table 1 Tab1:** OncoSNIPE study inclusion and exclusion criteria

**Inclusion criteria**	
General inclusion critreria	Adult patient, 18 years of age or older
	Naive chemo patient
	Performans status: 0,1 or 2
	Life expectancy > 3 months
	Subject affiliated to a social security and health insurance scheme
	Subject having dated and signed informed consent
	For women of childbearing age (negative pregnancy test): effective contraception
Specific inclusion criteria for Pancreatic ductal adenocarcinoma	Patient with histologically proven PDAC or Patient receiving a biopsy, as part of the usual care of the patient: Either from the primary tumor, Either a metastasis for a strong suspicion of locally advanced or metastatic PDAC
	With advanced or metastatic tumors (liver, lungs, peritoneum, others) that cannot benefit from local or locoregional treatment;
	Presence of target lesion (s) measurable according to RECIST criteria
	Patient who cannot be treated by surgery or radiotherapy
	Rate of tumor cells observed on FFPE biopsies must be ≥ 30%, otherwise, microdissection enrichment must be carried out to reach this threshold
Specific inclusion criteria for Lung cancer	Patient with histologically proven non-small cell lung cancer
	Locally advanced stage IIIB or IV
	Treatment with chemotherapy, targeted therapy, immunotherapy
	Tissue available after analysis of the usual biomarkers in the event of a non-epidermoid tumor
	Rate of tumor cells observed on FPPE biopsies must be ≥ 30%
	Presence of measurable target lesion or disease assessable according to RECIST criteria
Specific inclusion criteria for Breast cancer	Breast cancer of recent diagnosis, histologically proven
	Triple negative breast cancer: negativity of estrogen and progesterone receptors in the tumor (< 10%), absence of HER2 overexpression according to the IHC classification (score 0 or 1 +) and / or FISH negative or LumB: RO positive, RP positive or negative, HER2 negative, high proliferation;
	Stage I to III for triple negative breast cancer (including stage T4d = inflammatory cancer), Stage II or III of the UICC classification for LumB
	Non-metastatic patient (M0 according to TNM classification)
	Rate of tumor cells observed on FFPE biopsies must be ≥ 30%
	Patient who cannot be treated exclusively by surgery or radiotherapy

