### Study objectives and endpoints

The main objective of this study is to identify biomarkers of resistance to treatment in patients with triple negative or Luminal B breast cancer, locally advanced or metastatic non-small cell lung cancer or PDAC.

Analyses will be performed in each cohort independently. The primary endpoint will be a combinatory analysis of genomic, transcriptomic, clinical, medical images and immunological profile realized by ELISA and NGS (Next Generation Sequencing; Exome-seq, RNA-seq). Markers can be early or late biomarkers. The early markers will be markers present at baseline, the late markers will be the ones appearing during the follow-up. Resistance is defined as a tumoral nonresponse according to the RECIST (Response Evaluation Criteria In Solid Tumor) criteria or absence of Pathologic Complete Response (pCR).

The secondary objectives are to (i) identify therapeutic targets; (ii) determine the prognostic impact of the resistance markers on progression-free survival (PFS) and overall survival (OS),with PFS defined as the time between inclusion and progression (according to RECIST criteria or pCR) or death whatever the cause, and OS defined by the time between inclusion or death whatever the cause; (iii) identify the clinical, biological and/or genomic characteristics of long survivors (ie Patients who are still responding to the first line of treatment at the end of the 2-year follow-up.

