### Sample size

PDAC axis:

The expected response rate at 2 months is 30%.The probability modelized is non response to treatment with the assumption of an area under the ROC (Receiver Operating Characteristic) curve (AUC, Area Under de Curve) between 80 and 85%, a number of 200 subjects, i.e. 60 responders and 140 resistants (non-responders) will allow us to reach a power between 82 and 100% to prove a difference of 0.10 to 0.15 points against a theoretical AUC of 0.70, with a unilateral alpha risk of 5%.

To get 200 assessable patients for PDAC axis, a total of 400 patients should be included to anticipate a rate of non-evaluable patients of 50%.

Patients not assessable for the pancreas axis will be replaced and are defined as follows: premature exit (death) from study before treatment, patient who received less than 2 treatment cycles, patient who left studies prematurely before carrying out the efficacy visit (2 months after the start of treatment) or progression and patient with unsuccessful PDAC-derived organoid development.b)Lung cancer axis:

The expected response rate at 2 months is 30%. The expected response rate at 2 months is 30%. The probability modelized is non response to treatment with the assumption of an area under the ROC curve (AUC) between 80 and 85%, a number of 200 subjects, i.e. 60 responders and 140 resistants (non-responders) will allow us to reach a power of between 82 and 100% to prove a difference of 0.10 to 0.15 points against a theoretical AUC of 0.70, with a unilateral alpha risk of 5%.

To get 200 assessable patients for lung cancer axis, a total of 260 patients should be included to anticipate a rate of non-evaluable patients of 30%.

Patients not assessable for the lung axis will be replaced and defined as follows: prematurely exit (death) from study before treatment, patient having received less than 2 treatment cycles, patient who left studies prematurely before carrying out the efficacy visit (3 months after the start of treatment) or progression (excluding patients always responding after 24 months of follow-up).iii)Breast cancer axis:

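### Lung patients without a measurable lesion can count as RECIST responders only by complete response, so partial shrinkage in them is likely to be labelled resistance

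*Protocol article*

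**What the plan says.** Four statements in the protocol article bear on this point.

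- **Eligibility, lung (Table 1).** The criterion is "Presence of measurable target lesion or disease assessable according to RECIST criteria".
- **Eligibility, PDAC (same table).** The criterion is "Presence of target lesion (s) measurable according to RECIST criteria", with no alternative route.
- **Outcome label (Study objectives and endpoints).** Resistance is RECIST non-response or absence of pCR. The lung axis enrols stage IIIB or IV disease, so in practice RECIST supplies its label.
- **Sample size, lung axis.** The expected response rate at 2 months is 30%, and "a number of 200 subjects, i.e. 60 responders and 140 resistants (non-responders) will allow us to reach a power of between 82 and 100" per cent. The test is "against a theoretical AUC of 0.70, with a unilateral alpha risk of 5" per cent, for a true AUC of 0.80 to 0.85. The two classes add up to all 200 assessable patients. The rule beginning "Patients not assessable for the lung axis will be replaced and defined as follows: prematurely exit (death) from study before treatment" goes on to list fewer than 2 treatment cycles and exit before the efficacy visit or progression. It has no item for absence of a measurable lesion.

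**The concern.** In RECIST, partial response is a percentage reduction in the sum of measured target lesions. This is general knowledge of the method; the article does not spell it out. A patient with only non-measurable disease has no such sum. That patient can be recorded as complete response, progression, or the category in between. With two classes and no exclusion, the in-between category falls naturally among the resistant, even when the disease has clearly shrunk.

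The error goes one way only, from true responder to resistant, and it depends on how the disease has spread. Two things are at stake. First, the resistant class is mixed with responders, which pulls the observed AUC down and costs power. Second, a marker of the spread pattern that leaves no measurable lesion becomes associated with the resistance label for a reason unrelated to resistance. A larger sample repairs the first but not the second, and the second matters more in a marker-discovery study.

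**Working it through.** **Inputs from the Sample size section (lung):** 140 resistant (the modelled event), 60 responders, null AUC 0.70, true AUC 0.80 to 0.85, one-sided alpha 5%.

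**Input not in the documents:** f, the share of the 200 lung patients without a measurable lesion. I use 5% to 30%.

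**Step 1: reproduce the planned power.** With the Obuchowski binormal variance, n₁ resistant, n₀ responders and k = n₀/n₁:

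- a = 1.414 × z(AUC)
- Var = 0.0099 × exp(−a²/2) × [(5a² + 8) + (a² + 8)/k] / n₁
- Power = Φ{[(AUC₁ − 0.70) − 1.645 × SE₀] / SE₁}, with SE₀ taken at AUC 0.70 and SE₁ at AUC₁

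For 140 and 60, SE₀ = 0.0406. SE₁ = 0.0359 at AUC 0.80 and 0.0320 at AUC 0.85.

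- AUC 0.80: (0.10 − 1.645 × 0.0406)/0.0359 = 0.92, power 82.2% (stated 82%)
- AUC 0.85: (0.15 − 1.645 × 0.0406)/0.0320 = 2.60, power 99.5% (stated 100%)

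The same formula gives 86.0% for the breast axis (100 and 100, AUC 0.80), where the plan states 86%. The Hanley–McNeil variance gives 88.8% for lung at AUC 0.80. That is off the plan's scale, so I do not use it.

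**Step 2: label the shrinkers as resistant.** Assume a 30% true response rate in patients with and without measurable disease, negligible complete responses among the latter, and planned values (30%, AUC) that refer to correctly labelled patients. Then:

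- mislabelled responders m = 60f
- coded responders 60 − m; coded resistant 140 + m
- observed AUC = (140 × AUC + 0.5 × m)/(140 + m), because a mislabelled responder compared with another responder is a coin toss

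Example, f = 10%: m = 6, the classes are 54 and 146, and AUC = (140 × 0.80 + 0.5 × 6)/146 = 0.788. SE₀ = 0.0418 and SE₁ = 0.0376, so power is 69%.

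| f | Responders / resistant | Observed AUC (true 0.80) | Power, true AUC 0.80 | Power, true AUC 0.85 |
|---|---|---|---|---|
| 0 | 60 / 140 | 0.800 | 82% | 100% |
| 5% | 57 / 143 | 0.794 | 76% | 99% |
| 10% | 54 / 146 | 0.788 | 69% | 98% |
| 20% | 48 / 152 | 0.776 | 55% | 92% |
| 30% | 42 / 158 | 0.766 | 42% | 82% |

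If 10% of the responders without a measurable lesion still register as complete responses, power at AUC 0.80 is 77%, 71%, 58% and 46% for f = 5%, 10%, 20% and 30%.

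**Step 3: leave these patients out of the classification, without replacement.** The classes become 60(1 − f) and 140(1 − f), and the AUC stays at its true value.

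| f | Responders / resistant | Power, true AUC 0.80 |
|---|---|---|
| 5% | 57 / 133 | 80% |
| 10% | 54 / 126 | 78% |
| 20% | 48 / 112 | 74% |
| 30% | 42 / 98 | 68% |

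At every f, a smaller but correctly labelled set gives more power than the full mislabelled one.

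**The case against.** A reader might infer that these patients are counted as resistant whatever the treatment achieves. The documents do not support that: complete response remains open to them, so some can still be responders.

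The coding of the in-between category is also an inference. The article gives no RECIST version, does not list the categories that make up non-response, and says a full statistical plan will be written before database lock. That plan, or the full protocol, may settle the matter. This stands. Still, the eligibility line, the two-class split and the non-assessable list are all stated here, and together they point to the resistant class unless another rule intervenes.

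A reader might also infer that the response rate must fall below the planned 30%. The 30% and the AUC range are planning values for an axis that already admits assessable disease. If they describe the outcome as it will be coded in that mixed population, the power loss is already allowed for. The dependence of the label on spread pattern would remain.

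Finally, f is unknown, nothing in the documents supports the upper values of the range, and at a true AUC of 0.85 power stays at 82% or more throughout. Accepting assessable disease is also a defensible way to broaden the cohort, since these patients inform PFS, OS and the samples taken at progression. All of this limits the size of the point. It argues for a change to the analysis set rather than a demand to change eligibility.

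**Conclusion.** The point holds as a weakness in how the stated rules combine, not as an error in a stated figure. In the lung axis, true partial shrinkage in patients without a measurable lesion is likely to be labelled resistance. The resulting bias has one direction and follows the pattern of disease spread. PDAC does not have the problem, because its criterion requires measurable lesions.

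The power cost is material only towards the low end of the planned AUC range, where it runs from about 6 percentage points (82% to 76%) at f = 5% to about 40 (82% to 42%) at f = 30%. These figures rest on the assumed f, on equal true response rates with and without measurable disease, on few complete responses, and on planning values that describe correctly labelled patients. The direction of the bias needs fewer assumptions: only that some of these patients shrink partially and are then coded as non-responders.

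**What to change.** Restrict the lung responder/non-responder classification, and so the primary AUC analysis, to patients with at least one measurable target lesion at baseline. Keep the other lung patients for PFS, OS and the analyses of samples taken at progression. Because the criterion is a baseline one, it does not depend on outcome and can be applied to patients already enrolled.

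The cost is one line defining the analysis set and fewer classifiable lung patients. Without replacement, power at AUC 0.80 is about 80%, 78%, 74% and 68% for f = 5%, 10%, 20% and 30%. Adding these patients to the non-assessable list, whose members are replaced, would restore 82% but needs more recruitment. On the plan's own 260, 260/(1 − f) is about 274, 289, 325 and 371. That is a trade-off for the sponsor.

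Aligning the lung eligibility line with the PDAC wording for future patients is optional. It would not help those already enrolled in this ongoing study.

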**Exclusion Criteria**	
General Exclusion criteria	History of chemotherapy (except adjuvant completed for more than at least 6 months) or radiotherapy
	Patient whose monitoring and treatment will not be carried out in the study health establishments;
	Tumor not histologically proven;
	Life expectancy of less than 3 months
	Pregnancy or breastfeeding
	Refusal to participate in the trial
	Persons deprived of their liberty, persons under guardianship or curatorship
	Inability to submit to the medical follow-up of the test for social or psychological reasons
	No affiliation to a social security scheme or state medical aid (AME) or universal medical coverage (CMU)
	Any condition for which participation in the protocol would present a risk or which would not make it possible to comply with the requirements of the protocol according to the investigator
	History of other cancers in the last 5 years except cervical cancer and skin cancer of the basal or epidermoid cells treated
	Known HIV seropositivity
Specific exclusion criteria for Pancreatic ductal adenocarcinoma	Other histologies: neuroendocrine cancer, acinary cell carcinoma, pancreatic metastasis of another cancer
	Patient who cannot benefit from chemotherapy (Performans status (PS) 3—4);
	Other progressive cancer during the management of PDAC;
	Co-morbidities: Significant and / or uncontrolled pathologies or other conditions that may affect participation in the study, such as: unstable angina, symptomatic or uncontrolled arrhythmia requiring treatment, uncontrolled hypertension, congestive heart disease class NYHA II, III or IV, myocardial infarction or stroke in the 6 months before the study; Active or uncontrolled infection or pathology (compromised) compromising the ability to assess the patient or allow the patient to complete the study; Benign illnesses not controlled or whose control could be compromised by the treatment under study, such as severe diabetes, not controlled by medical treatment
Specific exclusion criteria for Breast cancer	Non-operable or metastatic breast cancer
	History of breast cancer treated
	Co-morbidities: Significant and / or uncontrolled pathologies or other conditions that may affect participation in the study, such as: unstable angina, symptomatic or uncontrolled arrhythmia requiring treatment, uncontrolled hypertension, congestive heart disease class NYHA II, III or IV, myocardial infarction or stroke in the 6 months before the study; Active or uncontrolled infection or pathology (compromised) compromising the ability to assess the patient or allow the patient to complete the study; Benign illnesses not controlled or whose control could be compromised by the treatment under study, such as severe diabetes, not controlled by medical treatment
Specific exclusion criteria for Lung cancer	Small cell lung cancer
	Stage I to IIIa non-small cell lung cancer
	Treatment by curative radiotherapy or radio-chemotherapy

### Study objectives and endpoints

The main objective of this study is to identify biomarkers of resistance to treatment in patients with triple negative or Luminal B breast cancer, locally advanced or metastatic non-small cell lung cancer or PDAC.

Analyses will be performed in each cohort independently. The primary endpoint will be a combinatory analysis of genomic, transcriptomic, clinical, medical images and immunological profile realized by ELISA and NGS (Next Generation Sequencing; Exome-seq, RNA-seq). Markers can be early or late biomarkers. The early markers will be markers present at baseline, the late markers will be the ones appearing during the follow-up. Resistance is defined as a tumoral nonresponse according to the RECIST (Response Evaluation Criteria In Solid Tumor) criteria or absence of Pathologic Complete Response (pCR).

The secondary objectives are to (i) identify therapeutic targets; (ii) determine the prognostic impact of the resistance markers on progression-free survival (PFS) and overall survival (OS),with PFS defined as the time between inclusion and progression (according to RECIST criteria or pCR) or death whatever the cause, and OS defined by the time between inclusion or death whatever the cause; (iii) identify the clinical, biological and/or genomic characteristics of long survivors (ie Patients who are still responding to the first line of treatment at the end of the 2-year follow-up.

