The expected response rate at 2 years is 50%. The probability modelized is non response to treatment with the assumption of an area under the ROC curve (AUC) between 80 and 85%, a number of 200 subjects, i.e. 100 responders and 100 resistants (non-responders) will allow us to reach a power of between 86 and 100% to prove a difference of 0.10 to 0.15 points against a theoretical AUC of 0.70, with a unilateral alpha risk of 5%.

To get 200 assessable patients for breast cancer axis, a total of 230 patients should be included to anticipate a rate of non-evaluable patients of 15%.

Patients not assessable for the breast axis will be replaced and defined as follows: prematurely exit (death) from study before treatment, patient having received less than 2 treatment cycles, patient who left studies prematurely before carrying out the efficacy visit (3 months after the start of treatment) or progression (excluding patients always responding after 24 months of follow-up).

Non-assessable patients will be replaced.

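### The PFS definition lists pCR, the favourable outcome, as a way of establishing progression; breast-cohort PFS is therefore wrong as written, and partly circular if absence of pCR was meant

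*Protocol article*

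**What the plan says.** All the definitions stand in the protocol article under Study objectives and endpoints.

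- **Resistance:** "Resistance is defined as a tumoral nonresponse according to the RECIST (Response Evaluation Criteria In Solid Tumor) criteria or absence of Pathologic Complete Response (pCR". Reaching pCR is therefore a response.
- **Secondary objective (ii):** to "determine the prognostic impact of the resistance markers on progression-free survival (PFS) and overall survival (OS", with "PFS defined as the time between inclusion and progression (according to RECIST criteria or pCR) or death whatever the cause".
- **Secondary objective (iii):** long survivors are "Patients who are still responding to the first line of treatment at the end of the 2-year follow-up".

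Analyses are run separately for each cohort. No other section corrects the PFS wording or gives a progression rule for breast cancer. The Sample size section, breast axis, expects a 50% response rate at 2 years among 200 assessable patients, "i.e. 100 responders and 100 resistants (non-responders".

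**The concern.** A PFS event should be an unfavourable outcome that the patient has actually had. The parenthesis in the PFS definition puts pCR beside RECIST as a criterion for progression, yet one paragraph earlier it is the absence of pCR that is unfavourable. The two sentences cannot both stand.

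What is at stake is the PFS half of objective (ii). If pCR is coded as an event, the best responders get short PFS. If absence of pCR is coded as an event, the outcome used to find the resistance markers reappears inside the endpoint used to test their prognostic value. Because cohorts are analysed separately, the error would not be diluted by patients in whom pCR is not assessed.

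**Working it through.** **1. Which cohort is affected.** The article does not assign pCR to a cohort, so this is inferred from Table 1. Breast patients must be M0, and the exclusions include "Non-operable or metastatic breast cancer". PDAC patients must not be treatable by surgery. Lung patients have stage IIIB or IV disease. A pathological response assessment is therefore to be expected mainly in breast.

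**2. The two readings against the other definitions.**

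| Reading of the parenthesis | Who gets a PFS event without progressing | Conflict |
|---|---|---|
| pCR is an event (literal) | patients with pCR | Resistance definition, where pCR is response; objective (iii), where a pCR patient still responding at 2 years is a long survivor yet already has a PFS event |
| Absence of pCR is an event | patients without pCR | The event is one of the two items that define resistance, so marker against PFS is partly marker against itself |

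**3. The plan's own figure.** The breast axis states 86 to 100% power for an AUC of 0.80 to 0.85 against 0.70, one-sided 5%, with 100 per group. I used the Obuchowski binormal variance, with a = 1.414 × Φ⁻¹(A) and equal groups of 100:

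SE(A)² = 0.0099 × exp(−a²/2) × [(5a² + 8) + (a² + 8)] / 100

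- SE(0.70) = 0.0381, SE(0.80) = 0.0346, SE(0.85) = 0.0313.
- Power at 0.80 = Φ[(0.10 − 1.645 × 0.0381) / 0.0346] = Φ(1.08) = 86.0%.
- Power at 0.85 = Φ[(0.15 − 1.645 × 0.0381) / 0.0313] = Φ(2.79) = 99.7%.

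The stated power is reproduced. PFS does not enter it, so the defect leaves it unchanged.

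**4. Size in the breast cohort.** The inputs are:

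- From the Sample size section: 200 assessable patients and a 50% response rate.
- Assumed, because the article gives no figure: response equals pCR; pCR is assessed within the 2 years; the true 2-year rate of progression, recurrence or death is p = 10 to 40%; and the risk without pCR is r = 1 to 3 times the risk with pCR.

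Patients counted on pCR status alone: 200 × 0.50 = 100 under either reading.

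With equal groups, risk with pCR = 2p/(1 + r), and risk without pCR = r × 2p/(1 + r).

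| p | r | Risk with pCR | Risk without pCR | Literal reading: of 100, no true event | Absence reading: of 100, no true event |
|---|---|---|---|---|---|
| 10% | 1 | 10% | 10% | 90 | 90 |
| 10% | 3 | 5% | 15% | 95 | 85 |
| 40% | 1 | 40% | 40% | 60 | 60 |
| 40% | 3 | 20% | 60% | 80 | 40 |

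- True events: 200 × p = 20 to 80.
- Literal reading: total events are 100 plus the true events without pCR, that is 110 to 160. The pCR patients make up 100/160 to 100/110, about 62 to 91%. Of those 100 patients, 60 to 95 have no true event.
- Absence reading: total events are 100 plus the true events with pCR, that is 105 to 140. The non-pCR patients make up 100/140 to 100/105, about 71 to 95%. Of those 100 patients, 40 to 90 have no true event.

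**5. What partly circular means here.** Take the absence reading with r = 1, so that pCR status has no bearing on true events. All 100 patients without pCR would still be counted as events, against 10 to 40 of the 100 with pCR. That difference comes from the definition. It passes to a marker only as far as the marker tracks pCR.

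**The case against.** The strongest defence is that this is a wording slip in a condensed article. The resistance definition makes the intended direction clear, so nobody is likely to code pCR as a failure, and a full statistical plan is due before database lock. It is fair that the literal coding is improbable. But the obvious repair, reading in absence of pCR, gives the circular version, so the sentence has no sound reading. It is also a stated rule that a later plan could carry forward, not a detail left open.

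Several objections to size and reach do stand:

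- A reader might infer that exactly half the breast cohort gets a false event. The article does not support this. Its 50% is a response rate at 2 years and is never called a pCR rate, and some of the 100 would truly progress or die, so their event is mistimed and not false.
- A reader might infer that PFS simply recodes the primary endpoint. The article words that endpoint differently: "The primary endpoint will be a combinatory analysis of genomic, transcriptomic, clinical, medical images and immunological profile". Absence of pCR is one of two alternatives in the resistance outcome.
- A reader might infer that the marker result is reversed or guaranteed. RECIST progression and death remain in the composite, so it is distorted or partly circular, no more.
- A reader might infer that RECIST cannot work in breast after surgery. The article gives neither RECIST rules nor a surgery schedule, so the point does not rest on this.

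**Conclusion.** The PFS definition is wrong as written and should be corrected. Its literal reading contradicts the resistance definition and objective (iii); its alternative reading makes the PFS part of objective (ii) partly circular.

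The contradiction itself needs no assumption. That it falls mainly on the breast cohort is inferred from eligibility. The size is conditional: if the 50% response rate is the pCR rate, about 100 of 200 assessable breast patients are counted on pCR status alone, and roughly 40 to 95 of them have no true event within 2 years across assumed event rates of 10 to 40% and risk ratios of 1 to 3. A different pCR rate would change these counts.

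The reach is limited to PFS in a secondary objective. The primary AUC sample size and OS are not affected.

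**What to change.** Remove pCR from the PFS definition. Keep RECIST progression or death for the PDAC and lung cohorts. For breast, state the event explicitly: progression, locoregional or distant recurrence, or death from any cause. Leave pCR where it belongs, in the resistance definition.

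The cost is about one sentence of endpoint wording, with no change to sample size or power. The article already plans 2 years of follow-up, sampling at progression and collection of disease evaluation reports. It does not name recurrence as a data item, so the sponsor should confirm that the CRF records its date and site. The change should be made before the statistical plan is finalised.

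Separately, the OS definition joins its start and end points with the word or where and is needed. That is a clerical slip and can be corrected in the same edit.
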